To develop a contextual history of factors that may have influenced implementation or outcomes at the community, district, provincial, and national levels, we will analyze qualitative data sources, including IDIs with health facility/systems staff (see Objective 2), IDIs with MWH governance and management structures (see Objective 2), and FGDs with relevant community members (see Objective 3). Throughout the project, we will also document, through project logs and meeting minutes, other events that occur that may affect the patterns of utilization or the effectiveness of our intervention, such as openings of new health facilities or redistricting of current ones.

#### Objective 7

To identify the key features of entrepreneurial strategies and management models developed to support the finances and operations of the Core Model, and to assess its effectiveness, we will use routinely collected monitoring data from registers, activity logs, training attendance logs, and the Core Model Checklist. From intervention sites, we will extract data from registers implemented by the project at the IGA (Main Cash book, Sales Journal and Monthly Goat Stock) to assess the revenue and expenses of the IGAs and MWH, quantity of products or services sold at the IGAs and stock at the goat rearing sites. For each type of IGA implemented, we will capture the costs of implementation, the MWH revenue over time from IGAs, community donations, or health facility contributions, and the proportion of MWH operating costs covered. Additionally, we will use program data to determine decisions made and changes occurring in MWH operating costs over time to understand what mix of operating costs and revenue streams create a financially sustainable MWH. We will triangulate findings with data from the semi-annual IDIs conducted with governance and management structures, IGAs staff/volunteers, and health facility staff (see Objectives 2 and 3).

For all qualitative data collection, all participants will be screened for eligibility and study staff will obtain informed consent. Study staff conversant in English and the appropriate local language, and trained in qualitative research methods and human subjects protection, will conduct the IDIs and FGDs. IDIs and FGDs will be recorded and transcribed verbatim, and translated to English when necessary.

### Inclusion criteria

Each data collection method will use its own set of inclusion and exclusion criteria as different participants will be enrolled depending in the method (Table 5).

**Table 5 Tab5:** Respondent Inclusion and Exclusion Criteria by Data Collection Method

Method	Respondents	Inclusion Criteria	Exclusion Criteria
MWH Experience Survey	Recent users of the MWH	• Mother utilizing the maternity home for at least 3 consecutive nights • Mother utilizing the home for maternal health services (ANC, labor or PNC visit) • Currently pregnant or under 6-weeks post-partum • >/= 15 years of age (emancipated minor)	• Has responded to the survey at a previous visit for the same maternal health services (ANC, labor or PNC) • Utilizing the home for reasons unrelated to maternal health • Unwilling or unable to provide informed consent
In-Depth Interviews	MWH Governance Committee & Management Unit Members; IGA Officer and SMAG Tailor	• Is a current governance committee/management unit member at an intervention site OR is responsible for overseeing MWH operations at a control site OR is an IGA Officer OR is a SMAG • Is capable of responding to the domains • >/= 18 years of age	• Is not currently affiliated with governance or management of MWH any of the study sites • Unwilling or unable to provide informed consent
Focus Group Discussions	Pregnant or RDW, Male with child < 1 year, Elders/mother in-law (MIL), SMAGs or other potential SMAG member including traditional birth attendant (TBA), community health worker (CHW), or any individual currently volunteering at the health centre in an MCH capacity	• Respondent is a SMAG member or other potential SMAG member including TBA, CHW, or any individual currently volunteering at the health centre in an MCH capacity, Elder or MIL in a study catchment area • Or is a pregnant woman or with a child under the age of 1 • Or is a male with a child under the age of 1, • >/= 15 years of age	• Has previously participated in a FGD in the same year at another site or in another category (i.e.: SMAG and recently delivered) • Is not currently affiliated with any of the study sites • Unwilling or unable to provide informed consent
IDI with Health Facility/System staff	Health Facility Staff and Health System Staff	• Is a current health facility staff member at any one of the study sites (intervention, control, CEMONC) • Is knowledgeable in maternal health capacity at the health facility • Or is knowledgeable in health facility financial records • Or is a district or provincial health officer in the study districts • >/= 18 years of age	• Is not currently affiliated with any of the study sites • Unwilling or unable to provide informed consent
Record Review	User of the health system/MWH	• Is recorded in MWH Register, Others Register or Activity Log between January 2016 – December 2018. • Is recorded in BEmONC facility-based data: Delivery Register, Maternity Ward Admission Register, Postnatal Care Register, Facility Transfer Log, Ante-natal care register (where applicable) and other improvised registers as necessary between January 2016 – December 2018.	• Was recorded in MWH or health facility registers before January 2016 or after December 2018

## Data management

Study staff will oversee data collection, entry, management and storage. Three of the registers (Delivery, Postnatal, and Referrals) are existing instruments implemented by the Ministry of Health (MoH). All other instruments discussed in this protocol were developed and will be implemented by the study team. To ensure quality for both project records and MoH registers, study staff will obtain permission from the MoH at the district levels to provide mentorship to health facility staff who complete the registers. During monthly data extraction visits, study team members will make note of specific gaps in the completion of each instrument and provide mentorship to address the gap. Gaps will be followed up the following month to ensure they are not persisting. Additionally, there will be some duplication of demographics across registers to allow for triangulation in the event of missing data.

All quantitative data will be captured using SurveyCTO Collect Software (Version 2.212; Dobility, 2017) installed on password protected tablets. The electronic survey forms will be encrypted and uploaded to a secure server upon completion, only accessible by the study team. Records from individual women will be linked through matching identifiable data fields (such as SMN, name, village, age, gravida, parity, delivery date), then women will be assigned a unique ID and identifiable information will be stripped and stored in a separate password protected linking file, only accessible by the study staff. Digital recordings will be downloaded to a password protected computer and paper copies of qualitative notes will be kept in a locked cabinet until they are fully transcribed, at which point audio files will be deleted and notes shredded. The qualitative transcriptions will not contain identifying information, only a unique study identification number. Only the study analytic team will have access to the data.

## Analysis

### Analytic framework

As described earlier, our Core Model for the MWH is theory-driven using the CFIR framework. We will use this framework to analyze data related to implementation effectiveness. To assess the aspects of sustainability, we will use the Sustainability Framework [18]. We want to know which types of programs and outcomes continue after the cessation of direct external support and under what circumstances. Sustainability outcomes are thought to be affected by processes that happen throughout the different phases of a project, especially the earlier phases, and the context of which it is implemented (social, policy, and financial environment) [18]. This framework will guide analysis of how components of the project may be contributing to sustainability of the MWHs.

### Quantitative analysis

Quantitative analyses will be conducted in SAS version 9.4 (SAS Institute, Cary, NC). Time-series data from utilization records will be analyzed using an interrupted time series analysis. Detailed analysis of quantitative data for specific tools is described below:

#### MWH experience survey

Survey data will be analyzed by calculating descriptive statistics stratified by intervention/control sites. We will also look for differences in indicators within the matched pairs. Categorical variables will be compared between intervention and control groups using the chi-squared test if cell sizes are sufficient or Fisher’s exact test if cell sizes are small; continuous variables will be compared using t-tests if normally distributed or non-parametric Wilcoxon rank sum tests if distribution is non-normal.

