### Study design and conceptual framework

We will use a mixed-methods approach and collect longitudinal, cross-sectional data at both the MAHMAZ intervention rural health center sites (*n* = 10) and the matched control sites (n = 10) before and during MAHMAZ project implementation, and for a short period (approximately 4 months) after cessation of project support.

Our study is guided by an integrated framework drawing from the Consolidated Framework for Implementation Research (CFIR) by Damschroder et al [19] and the Conceptual Framework for Sustainability of Public Health Programs (the Sustainability Framework) put forward by Scheirer and Dearing [18]. CFIR synthesizes constructs from multiple key implementation frameworks that are hypothesized to influence implementation. The Sustainability Framework posits the relationships between factors affecting sustainability and sustainability outcomes within a broader socio-political environment. Because these frameworks address different but related key drivers of program success – implementation and sustainability – elements from each underpin our study. We discuss these frameworks in more detail in the analysis section below.

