**Fig. 1 Fig1:**
[figure not shown]
Routine implementation data by category

**Table 2 Tab2:** Objectives, Questions, Data Sources for the MAHMAZ Implementation Effectiveness Protocol

Objective	Evaluation Questions	Data Sources
1. To assess the degree to which each individual intervention is effectively implemented according to the project plan and to document any adjustments and/or adaptations	a. At intervention sites, what is the proportion of MWHs that meet each component of the Core Model? b. What proportion of intervention sites are operating according to the project standard operating procedures?	**Quantitative** MWH Register Others Register MWH Activity Log MWH Experience Survey Core Model Checklist **Qualitative** Project records
2. To identify barriers and facilitators to implementation of the interventions	a. What are the barriers and facilitators to implementation of the: 1. Core Model? 2. Governance and management models? 3. IGAs?	**Qualitative** IDI with MWH governance and management structures IDI with IGA staff/volunteers IDI with health facility/system staff
3 To assess the extent to which implementation of the Core Model is perceived as responsive to community standards of acceptability by both the community and the women.	a. How does satisfaction with staying at the MWH compare in intervention sites relative to control sites? b. To what degree are the intervention MWH perceived as responsive to community standards and needs? c. What are the essential features and characteristic of the MWH as perceived by both women and communities? d. What are continued barriers to accessing and utilizing MWH after the intervention?	**Quantitative** MWH Experience Survey **Qualitative** IDIs with MWH governance and management structures FGDs with pregnant/ recently delivered women (RDW), men with children < 1, community el ders, Safe Motherhood Action Group members (S MAGs)
4. To assess the ways in which health facility-level factors change over the course of implementation.	a. How does capacity to handle obstetric emergencies change over time at the facility? b. How do staff perceptions of care related to maternal health change over time? c. What role does the MWH have in shaping staff perceptions of maternal health care?	**Quantitative** Health Facility Assessment **Qualitative** IDI with health facility/system staff

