In-depth Interviews	1) Provincial & District Government 2) Health Facility Staff 3) MWH Governance 4) MWH Management 5) IGA	Elicit information on the challenges, strengths, and perceived impact of the maternity home on the health facility staff and perceived patient behavior in terms of utilization, bypassing, etc. Also elicit perceptions of MWH within the health system and changes in prioritizing, financing, and planning for MWHs. Themes will include perspectives on governance and management challenges and successes, progress toward financial and operational sustainability, perspectives on community ownership of the MWH, MWH responsiveness to community needs/acceptability, and ideas for improvements. Elicit information on challenges and successes of the IGAs and perceived impact of the IGAs on the MWHs.	Every 6 months
Focus Group Discussions	1) Pregnant or women with a child under 1 year 2) Men with a child under age 1 3) Community elders or mother-in-law 4) SMAG members	The FGDs will elicit perspectives on: 1) the quality of the mothers’ shelters, 2) community ownership, 3) barriers and facilitators to access to care, 4) thoughts on sustainability, 5) thoughts on ways to improve each domain.	Once a year in 2016, 2017, and 2018
IGA-specific data collection tools			
Main Cashbooks	Maternity Waiting Home Main Cashbook	Extract information about the revenue and expenses for the MWHs and the IGAs.	Monthly collection of previous calendar month
Sales Journals	IGA Sales Journal	Extract information about the items sold at each IGA.	Monthly collection of previous calendar month
Monthly Goat Stock	Monthly Goat Stock Taking Book	Extract information about the change in goat numbers each month at the Goat Rearing IGAs.	Monthly collection of previous calendar month

**Table 4 Tab4:** Maximum Estimated Sample Size by Data Collection Method for the MAHMAZ Implementation Effectiveness Protocol

Method	Sample Size	Rationale
MWH Experience Survey	2880	A maximum of 6 women per site × 20 BEMONC sites X 24 months.
IDI with MWH Governance and Management Units	300	6 IDIs (3 governance members and 3 management members) per site X 10 BEmONC Intervention sites X 5 semi-annual cycles (July 2016–June 2018). This is the estimated sample size, but we will quit if we reach saturation or predictability during any given semi-annual cycle.

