On a monthly basis, the Monitoring & Evaluation (M&E) research assistants will visit each site and will administer the MWH Experience Survey. This is a primarily quantitative instrument that captures women’s general perceptions of and experience in the MWH (or other facility-affiliated structure in control sites) as related to the Core Model domains; opportunity costs incurred while staying at the MWH; and intended future use. The MWH Experience Survey captures the domains of quality that the community members identified as important to them in the formative evaluation [9]. The survey captures whether or not a particular element of the Core Model: 1) was available to the waiting mother at the time of say; 2) was utilized by the waiting mother at the time of stay; and 3) the waiting mother’s perception of quality of each Core Model element. These data are important for monitoring whether or not the service is well-received by our population of interest and what changes could be made to improve implementation. At each site, study staff will use the MWH register to randomly select a sample of up to six women who have been at the MWH/existing structure for at least three consecutive nights on the day of the visit and have not previously participated in the survey.

We will implement a Core Model Checklist to determine the degree to which each of the sites is implementing elements of the Core Model and how standard of care compares at control sites. The Core Model Checklist includes the same domains and Core Model elements as the Experience Survey so as to facilitate comparison and be confident in our assessment of fidelity. The Core Model Checklist will be administered by study staff via an electronic data capture system installed on tablets on a monthly basis at the MWH and will collect information on infrastructure, equipment and supplies, functioning of the management structures, and linkages with the associated health facility. Study staff will observe the MWHs/existing structures and surrounding areas to assess quality and document any quality problems. Study staff will also document whether MWHs/existing structures are adhering to standard operating procedures and implementing elements of the Core Model.

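### The survey analysis names no test that uses the order of the answers, so graded quality and satisfaction ratings, if that is how they are recorded, would be compared as unordered categories

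*Protocol article*

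**What the plan says.** The Quantitative analysis section announces tool-by-tool detail. For the MWH experience survey it promises descriptive statistics by arm, a look at differences within matched pairs, and tests chosen by variable type. There are two types. For the first, "Categorical variables will be compared between intervention and control groups using the chi-squared test if cell sizes are sufficient", with Fisher's exact test otherwise. For the second, "continuous variables will be compared using t-tests if normally distributed or non-parametric Wilcoxon rank sum tests if distribution is non-normal". Ordered categories have no branch of their own.

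The text on Objective 1 lists three things captured for each Core Model element. Two are yes/no in form (available, used). The third is the woman's "perception of quality of each Core Model element". Table 2, Objective 3, question a, asks: "How does satisfaction with staying at the MWH compare in intervention sites relative to control sites". The survey is the only quantitative source listed for that objective. The article does not give the answer scale or the number of levels, and it does not say which branch these items take.

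**The concern.** Perceived quality and satisfaction are commonly recorded on a short graded scale. Such a rating is not continuous in the ordinary sense, so a literal reading of the two branches sends it to chi-squared or Fisher. Those tests give the same result however the categories are ordered. They spread their sensitivity over k-1 degrees of freedom for k levels, and their result carries no direction.

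Two things are at stake. A consistent move towards better ratings in the intervention homes is more easily missed. And a significant result can come from a change in shape, such as more answers in the middle category, that does not mean higher satisfaction. Question 3a asks how satisfaction compares between arms, so a shift up or down is the natural target.

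**Working it through.** **Inputs from the protocol article.** Table 4 gives the survey size as "A maximum of 6 women per site × 20 BEMONC sites X 24 months": 6 × 20 × 24 = 2,880, which reproduces the stated maximum. With 10 intervention and 10 control sites (Study design and conceptual framework), that is at most 1,440 women per arm and 6 × 24 = 144 per site.

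**Assumptions, none of them in the document.** Two-sided alpha 0.05; 3, 4 or 5 ordered levels; a shift in one direction (common odds ratio); independent women unless stated otherwise.

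**Step 1: same signal, different degrees of freedom.** Power = P(noncentral χ² with df and λ > critical value). A 1-df ordered test has 80% power at λ = (1.960 + 0.842)² = 7.85. For a pure ordered shift, the unordered test works with about the same λ on k-1 df:

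| Levels | df | Critical value | Power, unordered | Loss from 80% |
|---|---|---|---|---|
| 2 | 1 | 3.84 | 80% | 0 |
| 3 | 2 | 5.99 | 70.9% | 9.1 |
| 4 | 3 | 7.81 | 64.5% | 15.5 |
| 5 | 4 | 9.49 | 59.5% | 20.5 |

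Simulation at 240 per arm (3,000 runs for each number of levels) agrees: 72% against 81%, 65% against 80%, and 59% against 81%. Where the ordered test has 90% power, the loss for 3 to 5 levels is 6.5 to 16 points; at 99% it is 1.3 to 4.2.

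**Step 2: at the planned maximum.** With 1,440 independent women per arm and assumed answer distributions, power of chi-squared against Wilcoxon is as follows (losses taken before rounding):

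| Odds ratio | 3 levels | 4 levels | 5 levels |
|---|---|---|---|
| 1.2 | 62.6 v 72.7 (10.1) | 59.6 v 75.9 (16.3) | 56.0 v 77.1 (21.1) |
| 1.25 | 80.7 v 87.9 (7.2) | 78.7 v 90.2 (11.5) | 75.8 v 91.0 (15.2) |
| 1.3 | 91.8 v 95.7 (3.8) | 90.9 v 96.9 (6.0) | 89.2 v 97.2 (8.0) |
| 1.5 | about 0 | about 0 | 0.1 |

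The loss is also small when neither test has much power: 1.2 to 2.2 points at 240 per arm and odds ratio 1.1.

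**Step 3: clustering.** Design effect = 1 + (144 - 1) × ICC. For an assumed ICC of 0.01 it is 2.43, and 1,440 / 2.43 = 593 effective women per arm. For 0.05 it is 8.15, and 1,440 / 8.15 = 177. At 177 per arm and odds ratio 1.7, power is 64% v 73% (3 levels), 60% v 77% (4) and 57% v 78% (5). That describes an analysis that allows for site. A 5% test that ignores site would have a true two-sided error of 2 × P(Z > 1.96/√2.43) = 21% to 2 × P(Z > 1.96/√8.15) = 49%. This holds for a plain Wilcoxon test as much as for chi-squared.

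**Step 4: when the order does not help.** If answers spread out without shifting, the ranking of the tests reverses. In one assumed 5-level case at 240 per arm, chi-squared has 79% power and Wilcoxon 5%.

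**The case against.** The strongest reply is that the premise is inferred. The answer scale is not shown; the items could be yes/no, or scored as numbers. Analysts often treat ratings as scores, and a non-normal score would go to the Wilcoxon test that the article already lists. Assigning items to tests is ordinary detail for the full protocol or the SAP, neither of which is shown. Chi-squared is a valid omnibus test, and the stratified descriptive statistics would show the direction. The survey is also one source among several in a mixed-methods evaluation; the main trial's primary outcome is facility delivery.

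Much of this stands. The scale is unknown, so the loss can only be stated conditionally, and chi-squared is not an error on this ground. The tables do let a reader see direction, although the named test does not assess it.

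What does not stand is that the matter is merely left open. The article fixes a rule by variable type, and that rule ties Wilcoxon to continuous variables. If a rating can be read into either branch, the same item could go to an unordered test or to a rank test, with nothing stated in advance to settle which.

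A reader might infer that the Objective 3 comparison does lose 9 to 20 points of power. The document does not support that: it gives no number of levels, alpha, effect size or power target for this survey.

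**Conclusion.** The point holds as a conditional one about efficiency. The categorical branch names only unordered tests, so a rating on three or more ordered levels would, read literally, be compared without its order. The loss of about 9 to 20 points rests on 3 to 5 levels, a one-directional shift, two-sided alpha 0.05 and an ordered test near 80% power. Over other plausible inputs it runs from zero upward: nothing for two levels, and almost nothing at full size once the odds ratio reaches about 1.5.

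It would be wrong to conclude that chi-squared is invalid because it ignores order, or that changing to a rank test alone would repair the comparison. Dependence between women at the same site is the larger problem for these tests, and an ordered test that ignores site leaves it in place.

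**What to change.** In the MWH experience survey analysis, divide categorical variables into binary or nominal and ordered. State that ordered quality and satisfaction ratings will be compared with an order-respecting analysis that accounts for site and matched pair. Two options are the mean rating per site compared between arms within the 10 pairs, or a proportional-odds model with site as a cluster. Report a directional effect (mean difference or common odds ratio) with a 95% CI, next to the table of categories by arm. Keep chi-squared/Fisher-type comparisons for binary items, such as availability and use, and for nominal items. If the ratings turn out to have two levels, saying so settles the point.

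The cost is a sentence or two and no new data. The downsides are a scoring or proportional-odds assumption and less sensitivity to a change in spread without a shift; the category table would show such a change.
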